## Abstract

**Background:**

Vitamin D deficiency (VDD) is associated with an increased risk for lifestyle-related diseases. In Japan, VDD is quite prevalent in all age groups, with its high risk in young women. Furthermore, its association during pregnancy with gestational hypertension and low birth weight has also been reported. VDD can be diagnosed by serum 25-hydroxyvitamin D [25(OH)D] levels, which, however, is not suited for screening. Therefore, we will create a predictive model for serum 25(OH)D concentration and prevalence of VDD based on such data as region, sun exposure habit, and vitamin D intake in young women.

**Methods:**

From 2020 to 2022, we conduct a cross-sectional study of 600 young women in four regions of Japan, identify the indices associated with serum 25(OH)D concentrations such as sun exposure habits, habitual vitamin D intake, ultraviolet-B irradiation, seasons (summer and winter) and latitude, and construct prediction models for serum 25(OH)D concentrations and VDD risk. This study has been registered with UMIN-CTR (ID: UMIN000041527).

**Results:**

One hundred and fifteen subjects have been collected from 6 institutions in winter as of May 2021. When data from more than 200 subjects have become available, we will conduct the interim analysis, summarize the data by region and facility, review the inclusion criteria for analysis, and check for missing values and outliers. Prediction models for serum 25(OH)D concentration and VDD will be determined in the final analysis when all cases have been collected.

**Conclusions:**

A screening tool for VDD risk to be developed in our study based on the predictive model would help the public and medical professionals prevent lifestyle-related diseases through improving VDD. Additionally, the results may serve as the scientific basis for determining the appropriate vitamin D intake and sun exposure standards.

## Introduction

Vitamin D insufficiency/deficiency increases the risk of various diseases, such as osteoporotic fracture, infectious diseases, diabetes mellitus, cardiovascular diseases, and cancer, and their primary prevention through improving vitamin D status can play pivotal roles [1]. Although attention has been mainly paid to reducing the elderly musculoskeletal syndromes by vitamin D, it can also play important roles in the various aspects of health promotion in younger subjects [2–5].

Considering the high prevalence of vitamin D insufficiency/deficiency in almost all age groups in Japan [6–8], its improvement is of utmost importance for preventing the above-mentioned diseases. To develop a strategy to ameliorate vitamin D insufficiency/deficiency, it is required to detect the factors related to serum 25-hydroxyvitamin D [25(OH)D] concentration, which is the best indicator of vitamin D nutritional status.

Serum 25(OH)D concentrations reflect not only the vitamin D intake but also the production in the skin by UV irradiation [9]. Since Japan has marked seasonal variation in climate and regional divergence in latitudes, a study covering multiple seasons and residential latitudes is needed. However, there have been few reports of studies conducted in different residential latitudes in Japan, and they are limited to reports on children and pregnant women [10,11]. On the other hand, there are some studies in Europe demonstrating that calculated UV irradiation levels is an important predictor for serum 25(OH)D concentrations [12,13].

Maternal vitamin D status has been reported to be significantly associated with fetal and neonatal vitamin D status and can affect the outcomes during pregnancy and neonatal and infant development [14]. For example, vitamin D deficiency (VDD) during pregnancy was significantly associated with pre-eclampsia [15–17], gestational diabetes [16], preterm birth, and small-for-gestational-age (SGA) [18]. Therefore, normalization of serum 25(OH)D levels in women of childbearing possibility is very important for safe delivery and birth health.

Based on such background, the present study will collect data on the seasons, lifestyle, and dietary habits associated with serum 25(OH)D concentrations in 600 young women from four different latitudes to identify predictors of serum 25(OH)D concentrations and develop a predictive model for vitamin D deficiency.

## Materials and methods

### Study design and participants

This is a cross-sectional study. Because of the potential influence of latitude in predicting serum 25(OH)D concentrations, we plan to recruit 600 healthy women between the ages of 18 and 40 years living in Japan, who participate in the study from November 2020 to September 2022 from four regions: Hokkaido/Tohoku, Kanto, Chubu/Kinki/Shikoku, and Kyushu/Okinawa. The prefectures and their latitudes included in this study are shown in Fig 1.

**Fig 1 pone.0264943.g001:**
[figure not shown]
Prefectures and their latitudes included in this study. Prefectures included in the study are indicated by points. The figure created by Authors based on map of Japan (Source: Geospatial Information Authority of Japan website (https://maps.gsi.go.jp/#6/38.125915/135.307617/&base=blank&ls=blank&disp=1&lcd=blank&vs=c0j0h0k0l0u0t0z0r0s0m0f0&d=m).

Women aged 18 and 40 years at the study entry and who have given voluntary written consent to participate in this study are being enrolled. Participants with comorbidities such as chronic kidney disease, autoimmune disease, cancer, liver disease, diabetes mellitus, and those under sun exposure restriction due to such diseases as xeroderma pigmentosum are excluded. Those with chronic gastrointestinal diseases such as celiac disease, chronic pancreatitis, inflammatory bowel disease, and cystic fibrosis are also excluded considering its possible interference with vitamin D absorption.

This study is conducted in two seasons: summer (June to September) and winter (December to February), each corresponding to the highest and lowest serum 25(OH)D values, respectively [19,20].

The participants are asked to fill out a questionnaire about their dietary history and habitual lifestyle during the week prior to their blood draw. Participants’ blood samples are collected in the morning and stored at 4 to 10°C in the refrigerator before centrifugation. Biochemical tests are performed on the next day, and then the residual serum samples are stored at -80°C for the measurement of serum 25(OH)D concentration. The study schedule is shown in Fig 2.

**Fig 2 pone.0264943.g002:**
[figure not shown]
The study schedule in each season. A cross-sectional study is conducted for 600 young women in four regions (Hokkaido/Tohoku, Kanto, Chubu/Kinki/Shikoku, and Kyushu/Okinawa) of Japan from 2020 to 2022. This study is performed twice in the summer (June to September) and in the winter (December to February) in each region. The figure describes the study schedule in each season.

Both a comprehensive self-administered diet history questionnaire (DHQ) and the Lifestyle Questionnaire assess habitual food intake and sun exposure over the past month, based on that serum 25(OH)D concentrations reflect the vitamin D status for approximately one month.

### Ethical considerations and registration

This study conforms to the Ethical Principles for Medical Research Involving Human Subjects issued by the Ministry of Health, Labour and Welfare and the Ministry of Education, Culture, Sports, Science, and Technology in Japan. This research protocol has been approved by the ethics committees at institutions written below;

1. The committee on research ethics, The Graduate School of Comprehensive Rehabilitation Osaka Prefecture University, August 3, 2020 (the date of approval), 2020–302 (the approval number), 2. The ethical committee in Osaka Shoin Women’s University, Feb 10, 2021 (the date of approval), 20–15 (the approval number), 3. The research ethics review committee of Kagawa Nutrition University, November 18, 2020 (the date of approval), 308 (the approval number), 4. The ethics committee of human research of Kobe Women’s University, December 4, 2020 (the date of approval), 2020-17-2 (the approval number), 5. The research ethics committee of Mukogawa Women’s University, November 25, 2020 (the date of approval), 20–64 (the approval number), 6. The committee on research ethics, University of Nagasaki, October 7, 2020 (the date of approval), 439 (the approval number), 7. The committee on research ethics, Kagoshima Women’s College, October 1, 2020 (the date of approval), R2-1 (the approval number), 8. The human research ethics committee of Nakamura Gakuen University, December 4, 2020 (the date of approval), 20–012 (the approval number), 9. The ethics committee of Tenshi College, October 12, 2020 (the date of approval), 2020-21(the approval number).

This study has been registered with UMIN-CTR (ID: UMIN000041527).

### Planned size

The sample size required for this study was calculated to be 600 cases; based on a previous study showing that 52% of females aged 17–18 years had VDD (serum 25(OH)D level below 20 ng/mL) [8], and assuming that the proportion of VDDs is also 50% in the study population, we expect 300 individuals to have VDDs. Finally, we expect 30% of the subjects to drop out of the study due to incomplete data sets and withdrawal of consent.

### Dietary assessment

A dietary assessment is performed. Trained research staffs check the participants’ answers to a comprehensive self-administered diet history questionnaire (DHQ) and resolve the ambiguity. Vitamin D intake is calculated by the revised comprehensive self-administered DHQ, which is a semi-quantitative questionnaire assessing habitual dietary intake over the past month, and already validated in previous studies [21–23]. Vitamin D intake is energy intake- adjusted by the density method and expressed as an amount (μg) per 1000 kcal of daily energy intake [24]. Estimates of habitual daily intake of energy, nutrients, and foods are calculated based on the Standard Tables of Food Composition in Japan [25].

### The questionnaire on habitual lifestyle including sun exposure and sunscreen use

The questionnaire on habitual lifestyle is studied as in “Indices obtained from a questionnaire response” of Table 1 and S1 File. S1 File is used in the present study. Investigation items include characteristics of the subjects, habitual sun exposure, and habitual dietary intake. These items were adopted from the recently developed “Vitamin D Deficiency Questionnaire for Japanese: VDDQ-J” [20]. We have not performed a pre-test for the questionnaire employed in the current study. However, VDDQ-J, which constitutes the basis for the current questionnaire has been validated and already published [20]. The vitamin D abundant fish was defined as fish containing more than 10 μg of vitamin D in the habitual intake value of Japanese, such as salmon, sardine, saury, flounder, eel, herring, and grunt.

**Table 1 pone.0264943.t001:** Demographic characteristics and questionnaire response.

Items	Category to be counted (unit to be summarized)
**Indices to be measured or calculated**	
** 1. Biochemical indices** ** **Serum 25(OH)D	(ng/mL)
** **Serum intact PTH	(pg/mL)
** 2. UV-B exposure related index** ** **The UV-B irradiation	(mJ/cm^2^)
** 3. Energy and Nutrients intakes (**calculated from DHQ)	
** **Energy	(kcal/day)
** **Protein	(g/day)
** **Fat	(g/day)
** **Carbohydrates	(g/day)
** **Calcium	(mg/day)
** **Calcium adjusted for energy intake	(mg/1000 kcal)
** **Vitamin D	(μg/day)
** **Vitamin D adjusted for energy intake	(μg/1000 kcal)
**Indices obtained from a questionnaire response** ** 1. Characteristics of the Subject** ** **Age	(y)
** **The residential area	
	Hokkaido Tohoku
	Kanto
	Chubu
	Kinki
	Chugoku, Shikoku
	Kyushu and Okinawa
** **The season of blood draw	Summer (July to September)
	Winter (December to February)
** **The Fitzpatrick skin type	I: Pale white skin, blue/green eyes, blond/red hair (Always burns, does not tan)
	II: Fair skin, blue eyes (Burns easily, tans poorly)
	III: Darker white skin (Tans after initial burn)
	IV: Light brown skin (Burns minimally, tans easily)
	V: Brown skin (Rarely burns, tans darkly easily)
	VI: Dark brown or black skin (Never burns, always tans darkly)
** **BMI (kg/m^2^)	<25 kg/m^2^
	≥25 kg/m^2^
** **Medical history	Hypertension
	Dyslipidemia
	Diabetes mellitus
	Liver diseases
	Renal diseases
	Thyroid disease
	Anemia
	Allergic disease
** **Medication	Yes
	No
** **Supplement use	No
	Vitamin D
	Calcium
	B vitamins
	Vitamin C
	Multivitamin
	Iron
	Others
** **Smoking status	Never smoked
	Formerly smoked
	Currently smoking
** **Alcohol consumption	Never
	Less than once per month
	2 to 3 times per month
	2 to 3 times per week
	More than 4 times per week
** **Sleeping hours	Over 9 hours
	8 hours
	7 hours
	6 hours
	Less than 5 hours
** **Exercise habit	More than twice per week
	Once per week
	1 to 2 times per month
	Rarely
**2. Habitual sun exposure** ** **Suntan within the past 12 months	Yes
	No
** **Sun exposure in the last 3 months	Always
	More often than not
	Sometimes
	Infrequently
	Never
** **Time regularly spent outside on weekdays (min) * Even outside, time spent in the trains or cars is not included because of the UV-B’s limited penetration of glass.	7 to 8 AM
	8 to 9 AM
	9 to 10 AM
	10 to 11 AM
	11 to 12 AM
	12 AM to 1 PM
	1 to 2 PM
	2 to 3 PM
	3 to 4 PM
	4 to 5 PM
	5 to 6 PM
** **Time spent outside on weekdays	≥3 h/d
	2 to <3 h/d
	1 to <2 h/d
	<1h/d
	rarely
** **Time regularly spent outside on weekends (min) * Even outside, time spent in the trains or cars is not included because of the UV-B’s limited penetration of glass.	7 to 8 AM
	8 to 9 AM
	9 to 10 AM
	10 to 11 AM
	11 to 12 AM
	12 AM to 1 PM
	1 to 2 PM
	2 to 3 PM
	3 to 4 PM
	4 to 5 PM
	5 to 6 PM
** **Time spent outside on weekends	≥3 h/d
	2 to <3 h/d
	1 to <2 h/d
	<1h/d
	rarely
** **Sunscreen use	Never (less than 1 day a week)
	Rarely (1 or 2 days a week)
	Sometimes (3 or 4 days a week)
	More often than not (5 or 6 days a week)
	Always (everyday)
** **Sunscreen use for arms and legs	No
	Yes
** **Paying attention to UV exposure	No
	Yes
** **Recently wearing clothes	Arms and legs exposed
	Without skin exposed
**3. Habitual dietary intake** ** **Habitual intake of fish	More than 4 days a week
	2 to 3 days a week
	1 to 2 days a week
	Less than 1 day a week
** **Habitual intake of the vitamin D abundant fish (e.g. salmon, sardine, saury, flounder, eel, herring and grunt)	More than 4 days a week
	2 to 3 days a week
	1 to 2 days a week
	Less than 1 day a week

### Assay of serum 25(OH)D concentration

Serum vitamin D metabolites are measured by liquid chromatography tandem mass spectrometry (LC-APCI-MS/MS) as previously described with some modification [26], i.e. derivation of extracted vitamin D metabolites with by 4-[2-(6,7-dimethoxy-4-methyl-3-oxo-3,4-dihydroquinoxalyl) ethyl]-1,2,4-triazoline-3,5-dione (DMEQ-TAD) in order to obtain the high sensitivity by increasing ionization efficiency [27]. Coefficient of variation (CV) for intra- and inter-assay were 3.4−9.2% and 11.9% for 25(OH)D, and 13.1−19.3% and 14.7% for 24,25(OH)_2_D, respectively. Total serum 25(OH)D level is calculated by their summation. VDD refers to 25(OH)D level less than 20 ng/mL. Serum intact parathyroid hormone (iPTH) is measured by electro chemiluminescnce immunoassay at SRL, Inc. (Tokyo, Japan).

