### Statistical analysis

The continuous variable will be expressed as mean ± standard deviation or median (interquartile range), and a categorical variable as frequency (percentage). Mann-Whitney U test and Kruskal-Wallis test will be used for the comparison between two groups and more than two groups, respectively. The chi-squared test will be used for categorical data.

An interim summary will be performed when the number of registered cases exceeds 200. The data will be summarized by region and institution. The inclusion criteria for analysis will be reviewed. We will also check for missing values and outliers. Predictors and prediction models will be determined in the final analysis when all cases have been collected.

Multivariate linear and logistic regression models are used to determine the predictors and predictive models for serum 25(OH)D concentration and VDD as outcomes, respectively. The regression coefficients and odds ratios will be calculated, and their 95% confidence intervals and p-values by Wald test will be calculated. Candidate predictors include age, residential area, skin type, smoking status, medication history, habitual drinking, physical activity, the season of blood collection, habitual sun exposure time and frequency, sunscreen use, the experience of suntan within the past 12 months, vitamin D supplement use, the habitual avoidance of sun exposure with parasol use or wearing long sleeve clothes, weekly frequency of vitamin D abundant fish consumption, and cumulative ambient UV-B irradiation.

Two-thirds of the randomly selected data will be used to build the predictive model, and the remaining data will be used to validate the built model. In the test set, variables shown to be significant in the univariate analysis and previously reported predictors are inserted into the multivariate model to construct the predictive model. In the validation set, the predictive performance of the prediction model is checked with the degrees of freedom-adjusted R-squared or AIC for linear regression analysis, and with the c-index for logistic regression analysis. In addition, as model calibration, the predicted and observed values are compared using Cook’s D for linear regression analysis and Hosmer-Lemeshow test for logistic regression analysis. Reporting on the construction of the predictive model will be done following the TRIPOD statement [32].

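### As written, total 25(OH)D is the sum of 25(OH)D and 24,25(OH)2D, which conflicts with defining VDD on 25(OH)D alone

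*Protocol article*

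**What the plan says.** All of the defining text is in the Protocol article, section Assay of serum 25(OH)D concentration.

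- It opens with the method: "Serum vitamin D metabolites are measured by liquid chromatography tandem mass spectrometry (LC-APCI-MS/MS"). The metabolites are not listed there.
- It then gives intra- and inter-assay CVs for two analytes, ending "11.9% for 25(OH)D, and 13.1−19.3% and 14.7% for 24,25(OH)_2_D, respectively".
- The next sentence is the calculation rule: "Total serum 25(OH)D level is calculated by their summation".
- The sentence after that sets the cut-off: "VDD refers to 25(OH)D level less than 20 ng/mL".

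Other sections use the result. Planned size applies the same 20 ng/mL limit to serum 25(OH)D and plans on half the women falling below it: "assuming that the proportion of VDDs is also 50% in the study population, we expect 300 individuals to have VDDs". Table 1 lists serum 25(OH)D and intact PTH as the only biochemical indices. The Statistical analysis section fits "predictive models for serum 25(OH)D concentration and VDD as outcomes, respectively".

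**The concern.** The two analytes named just before the rule are 25(OH)D and 24,25(OH)2D, so the natural reading of the sentence is that these two are added. The broader antecedent, the metabolites in the opening sentence, does not help, because it takes in 24,25(OH)2D as well. The D2 and D3 forms of 25(OH)D, the usual components of a total, are named nowhere in the article.

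As its name shows, 24,25(OH)2D carries an additional hydroxyl group. It is a separate metabolite and not a form of 25(OH)D. A total that includes it is not the quantity to which the 20 ng/mL limit is attached in the assay section and in Planned size.

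Both model outcomes depend on this one sentence, and so does the screening tool to be built from them. Planned size also assumes that half the women lie below the limit. The cut-off therefore sits at about the median, where a small upward shift reclassifies many women.

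**Working it through.** **Inputs from the article.** Planned N is 600, the assumed VDD share is 50%, and the cut-off is 20 ng/mL (Planned size; assay section).

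**Inputs assumed, because the article does not give them.** The ratio r of 24,25(OH)2D to 25(OH)D is taken as 2% to 15%, the same for every woman. 25(OH)D is taken as normal with SD 5 to 8 ng/mL. A mean of 20 ng/mL follows from 50% below 20 under a symmetric distribution.

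**The plan's own figure.** 600 × 0.50 = 300 women with VDD. This reproduces.

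**Effect of the rule if followed.** The computed total is 25(OH)D × (1 + r). A woman is then classed as VDD only if her 25(OH)D is below 20/(1 + r). The VDD share becomes

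Φ((20/(1 + r) − 20)/SD),

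and the number reclassified is 600 × (0.50 − share).

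Example, r = 10% and SD = 5: 20/1.10 = 18.18; (18.18 − 20)/5 = −0.364; Φ = 0.358; 600 × (0.50 − 0.358) ≈ 85.

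| r | Cut-off in 25(OH)D (ng/mL) | VDD share, SD 5 | VDD share, SD 8 | Women moved, of 600 (SD 8 to SD 5) |
|---|---|---|---|---|
| 2% | 19.61 | 46.9% | 48.0% | 12 to 19 |
| 5% | 19.05 | 42.4% | 45.3% | 28 to 45 |
| 10% | 18.18 | 35.8% | 41.0% | 54 to 85 |
| 15% | 17.39 | 30.1% | 37.2% | 77 to 119 |

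**Check with a lognormal distribution** (median 20, CV 25% to 40%). The share is 46.8–48.0% at r = 2% and 28.5–35.8% at r = 15%, which is about 12 to 129 women moved over the whole range. The conclusion does not depend on the normal shape.

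**Direction.** This needs no assumption about r or SD. Adding any positive amount raises the total, so a woman can leave the VDD group but cannot enter it.

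**The case against.** The strongest reply is that this is a dropped antecedent and not a chosen rule. The section heading, the name of the total, the VDD definition, Table 1 and the models all refer to 25(OH)D. 24,25(OH)2D appears only in the sentence on CVs. A sentence about the forms of 25(OH)D, shortened when the article was condensed, would fit that pattern well. The assay is also described by reference to earlier methods papers, which may set out the sum. This stands as far as it goes: the article does not show that the laboratory adds 24,25(OH)2D. It does not rescue the sentence, which states a calculation rule that conflicts with the article's own definition of VDD.

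Three stronger readings are tempting, and the article does not support them.

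- *The values already collected are wrong.* The article reports 115 cases collected and residual serum stored for later measurement. It does not say that any total has been computed.
- *The sum is a noisier outcome, because the added analyte has the larger CV* ("and 14.7% for 24,25(OH)_2_D, respectively" for inter-assay, against 11.9%). Take 25(OH)D at 20 ng/mL, r = 10% and independent errors. The SDs are 20 × 0.119 = 2.38 and 2 × 0.147 = 0.294. The SD of the sum is √(2.38² + 0.294²) = 2.40, and its CV is 2.40/22 = 10.9%, slightly below 11.9%. There is no precision argument.
- *The linear model would be spoiled.* With a fixed ratio, its coefficients and predictions are multiplied by 1 + r, while R-squared and p-values do not change. Predicted concentrations would be too high by that factor, but the main damage is to the VDD classification. The article also does not rank the two outcomes, so neither should be called primary.

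It is also fair to say that the size rests wholly on assumed values. At the low end of the range the effect is only 2 to 3 percentage points.

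**Conclusion.** The point holds as a conflict in the text. The printed rule for total 25(OH)D includes a metabolite that the VDD definition, Table 1 and the model outcomes do not. Whether any value is or will be wrong cannot be judged from the article.

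If the rule were followed, VDD would be under-counted, with certainty as to direction. Under the stated assumptions (fixed r of 2% to 15%, mean 20 and SD 5 to 8 ng/mL), prevalence would fall from 50% to 47–48% at r = 2% and to 30–37% at r = 15%. That is 12 to 119 of 600 women moved out of the VDD group. A screening model trained on those labels would predict too little deficiency. The sentence should be corrected: the possible consequence is large, laboratory practice is not stated, and the correction is cheap.

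**What to change.** Replace the sentence with one that names the components, for example: total serum 25(OH)D is the sum of 25(OH)D2 and 25(OH)D3; 24,25(OH)2D is measured separately and is not added; VDD is a total below 20 ng/mL. The investigators should confirm that these are the components the laboratory sums.

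Before the interim summary planned at more than 200 registered cases, ask the laboratory for its calculation in writing. If any samples have already been assayed, confirm that their totals follow the same rule, and recompute any that do not.

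The cost is one sentence and one laboratory query. The design, sample size and models need no change.
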